### Randomisation and blinding

After recruitment of the 24 sites to the study and collection of baseline (Time 1) data from all sites, the sites were allocated to either the intervention or control arm by a biostatistician ([name]) who was not involved in recruitment, data collection, or contact with the sites. Sites were stratified by type of aged care (RACF vs. CACS). Within each stratum, restricted randomisation was used to balance the groups by: size of the service (number of clients), span of control (care staff to middle management ratio), and geographical location (rural vs. urban) [28]. Location is balanced exactly, while for size and span of control the means of the two groups are allowed to differ by no more than 10% in relative terms (*i.e*., ratio of means between 0.9 and 1.1). Allocation was thus fully concealed. The sites were notified by email and completed a written agreement to abide by the random allocation. Also, in an attempt to reduce bias associated with staff becoming aware of managers attending the CLiAC program, participating managers signed forms agreeing not to discuss with their work teams and staff any group specific activities or training that have occurred, and agreed to maintain blinding until the end of data collection. The members of the research team responsible for data entry and analysis will remain blind until completion of the main analysis.

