### Participants and sampling frame

Participants are both the care staff and the middle managers of the targeted residential and community aged care services. The sample size calculation was based on the primary outcome, participants’ perceived work environment: the subscales of the Work Environment Scale-R (WES-R) [26]. The study has 80% power to detect a difference of 0.49 standard deviations between groups as significant at the 5% level. This assumes that at least 20 clusters (sites) each with a minimum of 30 participants will complete the study, and that the intra-cluster correlation coefficient (ICC) is 0.26 (average estimate from a recent nursing home staff training intervention carried out in England and Wales) [27], giving a design effect of 8.54. The detectable difference is consistent with the WES-R [26] test developer’s recommendation that half a standard deviation represents a meaningful change on the instrument ([name], personal communication, Dec. 4, 2008). Consequently, the study will be able to detect a meaningful difference between the trial groups, and it is practical and feasible in terms of study design and data collection.

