### Data analysis plan

Baseline data will be analysed descriptively by allocated group. All data will be analysed on an intention-to-treat basis (*i.e*., participants will be assigned to the site where they were employed at randomisation even if they subsequently moved to another participating site). Analyses will be performed by an analyst who was not involved in data collection and is blinded to group identification, using either SAS (SAS Institute, Cary, NC, USA) or Stata (StataCorp LP, College Station, TX, USA), and supervised by a biostatistician ([name]).

For the primary analysis, differences between intervention and control groups in the primary outcome at Time 3 will be analysed using linear regression models adjusted for stratification by type of aged care (RACF/CACS) and clustering by site. Other outcomes, such as those for H_2_ and H_3_, which are measured at the cluster level, will be compared by cluster-level analysis, for example, using a negative binomial model stratified by type. All outcomes will similarly be compared at Time 2 to determine the short-term effect of the intervention. In secondary analyses, potential confounders, both at the cluster and individual level, will also be adjusted for, including baseline values of the outcome variables. Potential individual-level confounders include age, gender, previous aged care training/education, and length of time participants have worked in aged care.

An economic evaluation of the CLiAC program will be undertaken using the costs and outcomes (consequences) data discussed above. The first task will involve identifying, measuring and valuing the relevant costs and consequences of the intervention and usual practice (control group). The total costs include the cost of the CLiAC program facilitator, expert education consultant, and educational material. Quantities of resource use will be measured and unit costs (prices) will be assigned, including the cost of mentoring the CLiAC facilitator and implementing the program, using current pay rates (see HR data provided by collaborating organisation) and commercial rates (prices). The outcomes to be explored in the evaluation are: (a) the scores on the work environment measure (WES-R), effectiveness of leadership style (MLQ), person-centred care (P-CAT), and workforce dynamics (WDQ) assessed by staff; and (b) staff turnover and absenteeism. All outcomes (consequences) will be measured in natural units.

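### The primary model omits location, service size and span of control, on which allocation was restricted; if these predict the outcome beyond type, the reported standard error may be too large

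*Protocol article*

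**What the plan says.** Under Randomisation and blinding, the protocol article stratifies the 24 sites by type (residential or community) and then restricts the allocation further: "Within each stratum, restricted randomisation was used to balance the groups by: size of the service (number of clients), span of control" and rural or urban location. On how tight the restriction is: "Location is balanced exactly, while for size and span of control the means of the two groups are allowed to differ" by at most 10% in relative terms, that is, a ratio of means between 0.9 and 1.1.

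Under Data analysis plan, the primary outcome at Time 3 is compared between arms with "linear regression models adjusted for stratification by type of aged care (RACF/CACS) and clustering by site". The bracket limits the stratification term to type. Other covariates come in only later: "In secondary analyses, potential confounders, both at the cluster and individual level, will also be adjusted for, including baseline values of the outcome variables". The Abstract gives the same division between primary and secondary analysis.

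The article does not say how clustering is handled (cluster-level regression, mixed model or cluster-robust standard error), nor how strongly the three factors relate to the outcome.

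**The concern.** Four site characteristics constrained the allocation, and one of them enters the primary model. Location, balanced exactly within type, acts as a second stratification factor but is not treated as one.

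Forcing the arms to be alike on a predictor removes that predictor's contribution to chance differences between arms, so the effect estimate varies less from one admissible allocation to another. A model without the predictor still counts its between-site variation as residual, so the standard error it reports is that of an unrestricted allocation. The confidence interval is then wider, and the p-value larger, than the design warrants.

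The number of sites limits this trial's power, so precision gained through the design but left out of the reported inference would matter. The article fixes the covariates of the primary model explicitly, so this is not a detail left open for an analysis plan.

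**Working it through.** **Inputs from the article.** 24 sites, 12 per arm, six of each type per arm; ICC 0.26; 30 participants per site; 5% level (taken as two-sided, which the article does not state); target difference 0.49 SD.

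**Assumption.** R2 is the share of between-site variance, beyond type, that location, size and span of control explain together. The article gives no figure, so a range is shown.

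**The plan's own figures.** The design effect reproduces: 1 + (30 − 1) × 0.26 = 8.54. The detectable difference does not. The article says "The study has 80% power to detect a difference of 0.49 standard deviations between groups as significant at the 5% level" and "This assumes that at least 20 clusters (sites) each with a minimum of 30 participants will complete the study". Twenty sites of 30 give 300 per arm, and 2.80 × √(2 × 8.54 / 300) = 2.80 × 0.239 = 0.67 SD. That is a separate issue; here it shows only that power is scarce.

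**Step 1: hand calculation with 24 sites and perfect balance.** In SD units, the variance of a site mean is 0.26 + 0.74/30 = 0.2847. The SE of the difference is √(0.2847 × (1/12 + 1/12)) = 0.218, and a type-only model reports about this value whatever R2 is. With the three factors accounted for, the site variance is 0.26 × (1 − R2) + 0.0247:

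- R2 = 0.1: √(0.2587/6) = 0.208; the type-only SE is 5% larger.
- R2 = 0.3: √(0.2067/6) = 0.186; 17% larger.
- R2 = 0.5: √(0.1547/6) = 0.161; 36% larger.

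The residual degrees of freedom fall from 24 − 3 = 21 (t = 2.08) to 24 − 6 = 18 (t = 2.10). Approximate power of the adjusted model at 0.49 SD is Φ(0.49/0.186 − 2.10) = Φ(0.53) ≈ 70% at R2 = 0.3, and Φ(0.49/0.161 − 2.10) = Φ(0.94) ≈ 83% at R2 = 0.5.

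**Step 2: simulation under the stated restriction.** 4,000 trials per setting; location exact and mean ratios of size and span of control within 0.9 to 1.1 in each type; spread of size and span and the rural share assumed; site-level regression with t tests.

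| R2 | Type-only: mean model SE / true SE | Type-only: type I error | Adjusted: type I error | Power at 0.49 SD, type-only / adjusted |
|---|---|---|---|---|
| 0 | 0.214 / 0.216 | 4.6% | 4.7% | 59% / 57% |
| 0.1 | 0.216 / 0.210 | 4.2% | 4.9% | 58% / 60% |
| 0.3 | 0.217 / 0.191 | 3.2% | 5.4% | 57% / 70% |
| 0.5 | 0.218 / 0.169 | 1.2% | 5.6% | 56% / 81% |

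The Monte Carlo standard error near 5% is √(0.05 × 0.95/4000) = 0.3 points. Two further simulations with their own assumed spreads put the type-only type I error at 2.3 to 2.4% for R2 = 0.3 and 0.8 to 1.1% for R2 = 0.5. One of them puts the loss of power from adjusting at R2 = 0 at about one point.

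**Step 3: the same trials with uncorrected cluster-robust standard errors.**

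| R2 | Type-only type I error, normal / t(23) | Adjusted type I error, normal / t(23) |
|---|---|---|
| 0 | 7.2% / 5.9% | 10.0% / 8.4% |
| 0.1 | 6.2% / 5.2% | 10.1% / 8.2% |
| 0.3 | 4.5% / 3.7% | 10.1% / 8.5% |
| 0.5 | 2.5% / 1.8% | 10.3% / 9.0% |

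**Step 4: lost sites.** Trial status reports two of 24 sites disqualified after Time 2. Dropping two intervention sites at random at R2 = 0.3 (3,000 trials, site-level t) left the type-only type I error at 2.6%, and power at 51% type-only against 65% adjusted.

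**The case against.** A reader might infer that the standard error simply is too large and the primary test conservative. The documents do not support that unconditional reading, for two reasons. It requires the three factors to predict staff-rated work environment after type is in the model, and the article offers no evidence on this; at R2 of 0 to 0.1 there is nothing to correct. It also depends on the unstated variance method. With uncorrected cluster-robust standard errors the type-only test is slightly liberal at low R2 (about 6 to 7%) and becomes conservative only at higher R2. Both objections stand.

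A reader might also say that the precision bought by the restriction is discarded. That goes too far. The estimate keeps its smaller true variance; only the reported standard error, interval and p-value fail to show it. The error does not create false positives under t inference.

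The remedy has a risk of its own: three more site-level covariates with uncorrected robust standard errors would inflate the type I error. This stands and shapes the fix.

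Finally, the secondary analyses may well include these factors as cluster-level confounders. Not listing them there is ordinary condensation in an article and no finding. The secondary analyses do not set the primary test, however, so the mismatch in the primary model remains.

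**Conclusion.** The point holds in conditional form. The primary model respects stratification by type but not the other three constraints on allocation. Under site-level t inference the consequence is nil or trivial at R2 of 0 to 0.1. Type I error is about 2 to 3% at R2 = 0.3 and about 1% at R2 = 0.5. The corresponding power at 0.49 SD, type-only against adjusted, is about 56% against 70%, and about 56% against 82%.

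These figures rest on the article's ICC of 0.26 and 30 participants per site, on assumed distributions of size, span and location, and on R2, which is unknown. This is a recommended gain in efficiency and in consistency between design and analysis. It does not threaten the validity of the effect estimate.

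**What to change.** Add location (rural or urban), service size (number of clients) and span of control to the primary model as site-level covariates alongside type, and state the small-sample inference. Two options fit: cluster-level regression with t on the residual site degrees of freedom, or a cluster-robust standard error with a bias correction. Alternatively, use a permutation test over the allocations that met the restriction criteria, which matches the inference to the design directly. Do not pair the adjustment with uncorrected cluster-robust standard errors.

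The cost is three site-level degrees of freedom (critical t from 2.08 to 2.10 with 24 sites, or 2.09 to 2.12 with 22) and about one point of power if the factors are not prognostic. No new data are needed, since the values were used for randomisation. The article reports that analysis had not begun and that analysts were blinded, so the change could be fixed in writing before unblinding.

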### Recruitment: middle managers and care staff

Recruitment of aged care middle managers and care staff to the study was based on the eligibility criteria shown in Table 1. All staff employed at each site at each data collection time were eligible to participate. An invitation letter and a set of questionnaires were sent to all eligible staff of the participating sites from the research team. Return of their questionnaire was considered as consent (implied consent).

### Measures and data collection

The primary study outcomes are: work environment for aged care staff, care quality and safety, and staff turnover rates. Secondary outcomes include aged care managers' knowledge and skills in leadership and management, aged care staff absenteeism, intention to stay or leave, stress levels, job satisfaction, and various costs including direct costs of recruiting and retaining aged care staff, and cost of resources used in care delivery covered by the aged care service provider.

### Aged care managers and care staff surveys

The self-administered outcome evaluation survey for managers and care staff combines both previously published and validated scales to measure the outcomes of interest. Table 2 provides details of the outcome measures included in the survey and how they relate to each of the hypotheses. In addition, the evaluation survey collates manager and staff demographic information including: age, gender, country of birth, year that employment commenced at the present service, current site and current job role, current title, programs involved in, employment status (full/part-time), professional background, experience in aged care/dementia care (years), highest level of education, aged care specific training, the type of dementia/aged care training or education completed, and the type of leadership/management training or education completed. The surveys were administered at baseline (Time 1), and repeated nine months from baseline (Time 2) and nine months after completion of Time 2 (Time 3). At Time 3, an additional two open-ended questions were added to the staff survey asking them to describe their experience of leadership and management at their site over the past six months and whether they have noticed any changes, plus a general comments question.

**Table 2 T2:** Outcome measures

**Instrument**	**Description of the instrument & domains**	**Hypotheses & measures**
Approaches to Dementia Questionnaire (ADQ) [29]	19 items that measure staff attitudes toward dementia care that reflects their understanding of the need to provide person-centred care for people with dementia. Likert scale ranging from 1 to 5 (strongly agree/disagree). Higher scores indicate a greater understanding of the need to provide person-centred care for people with dementia.	H_2_ – Care quality
Person-centred Care Assessment Tool (P-CAT) [30]	13 items that measure the extent to which staff rate their residential aged-care setting to be person-centred and providing best quality care for people with dementia. Responses are on a Likert scale ranging from 1 to 5 (‘disagree completely’ to ‘agree completely’). Higher scores indicate higher person-centred and quality care.	H_2_ – Care quality
Workforce Dynamics Questionnaire (WDQ) [31]	58 items across 11 domains that measure staff satisfaction, staff perceptions of care quality, access to technology and equipment and training and career progression opportunities. Responses are on a Likert scale ranging from 1 to 10 (‘strongly disagree’ to ‘strongly agree’). Higher scores indicate greater overall job satisfaction and greater perceptions of the quality of care provided, access to technology and equipment, training and greater perceived career progression opportunities.	H_5_ Intention to stay and to leave
		H_7_ – Job satisfaction
Work Environment Scale-R (WES-R) [26]	90 items that measure the perception of the respondents workplace environment including: (a) relationships (involvement, co-worker cohesions, supervisor support); (b) goal orientation (autonomy, task orientation, work pressure); and (c) system maintenance and change dimensions (clarity, managerial control, innovation and physical comfort). True or False response (1 = positive, 0 = negative, total ranging 0 to 90). Higher scores indicate a more positive perception of the workplace environment.	H_1_ – Work environment
		H_6_ – Stress levels
		H_7_ – Job satisfaction
Multi-factor Leadership questionnaire (MLQ)- Manager and Staff version [32]	46 items across 10 subscales that measure different types of leaders and differentiates between effective and non-effective leaders on a 5-point Likert scale ranging from (0 = not at all, 1 = once in a while, 2 = sometimes, 3 = fairly often, 4 = frequently, if not always). Individual aggregate scores for each of the leadership styles are calculated and higher scores indicate a greater tendency towards the particular style. An aggregate score for outcomes of leadership is also calculated, whereby higher scores indicate better perceived leadership including greater effectiveness and satisfaction.	H_1_ – Work environment
		H_9_ – Managers’ knowledge and skills in leadership and management

Distribution and collation of the baseline evaluation surveys occurred in two ways. First, a designated manager at each site was sent survey packs (including invitation letter, study information sheet and survey) to distribute to staff. Staff were then able to return completed surveys in a supplied prepaid self-addressed envelope to the research team. For sites with low response rates, a follow-up telephone call or email was sent to the managers and additional survey packs disseminated as required. Managers were requested to encourage staff to complete the survey, but it was made clear to the managers and staff that participation was not compulsory. Secondly, site visits by a member of the research team were also used to disseminate and collect the evaluation surveys during staff meetings or breaks. During the site visits, staff were able to complete the survey during work hours. Any staff members who were not present during the visit were given the survey to complete and return later.

### CLiAC program evaluation (H_9_ – Manager’s knowledge and skills in leadership)

Key questions from the NHS Leadership Centre Evaluation Questionnaire [33] and the CECCL Evaluation [22] were adapted for the evaluation of the CLiAC program concerning the impact and outcomes associated with the program. The final survey consists of a mix of quantitative questions using various Likert scale responses to review changes associated with the program including: managers’ perceptions of the CLiAC, perceived effects on quality of care, changes to practices and procedures, sustainability of change, improvements to and valued aspects of the program. The survey also has a number of open-ended questions that allow respondents to give feedback on how support for participants of the program might be improved and how the program could be improved overall. The survey takes approximately 40 minutes to complete, and was distributed at 3 months, 6 months and 12 months following completion of the program.

### Collation of human resource data (H_3, 4_ & _8_ – Staff turnover, absenteeism and costs)

Human resource data collected included information on staffing levels, resignations, absenteeism and recruitment. The information was supplied in aggregate form for each site (intervention and control) that took part in the study, for the duration of the study, by the collaborating organisation using a standardised template.

### Collation of data on quality indicators (H_2_ – Care quality and safety)

Quality indicator data included information on the number of unplanned hospital admissions, falls with injury, unintentional weight loss greater than two kilograms, new pressure areas, and new urinary tract infections [34]. These indicators were chosen for their appropriateness and relevance to both community and residential care settings and the fact that they were already part of the regular data collection of the collaborating organisation. Table 3 provides details of the clinical indicators. The data was collected monthly throughout the study (for a total period of two years) using a standardised spreadsheet. For each quality variable, a common set of criteria was detailed and provided to each site along with the spreadsheet. Senior management at all study sites collated the quality indicator data on the last day of each month and sent the spreadsheet to the research team.

**Table 3 T3:** Clinical indicators

**Indicators**	**Definition and criteria**
**Fall with injury**	A fall is an event that results in a person coming to rest inadvertently on the ground or floor or other lower level. If a client is found on the floor or ground, it should be assumed that they have fallen (unless they are cognitively unimpaired and indicate that they put themselves there on purpose). Signs of injury may include fracture, bruises, skin tears, sprains, lacerations, reddened areas or aggravation of pre-existing complaints such as back pain.
**New urinary track infection**	If the resident does not have an indwelling catheter, they must have at least three of the following signs or symptoms:
	1. Fever (greater than 38°C) or chills;
	2. New or increased burning pain on urination, frequency or urgency;
	3. New flank or suprapubic pain or tenderness;
	4. Change in the character of urine;
	5. Worsening of mental or functional status;
	6. New or increased incontinence.
	If the resident has an indwelling catheter, they must have at least two of the following signs or symptoms:
	1. Fever (greater than 38°C) or chills;
	2. New flank or suprapubic pain or tenderness;
	3. Change in the character of urine;
	4. Worsening of mental or functional status.
**New pressure areas**	A pressure ulcer is defined as ‘any lesion caused by unrelieved pressure, resulting in damage of the skin and underlying tissue.’ Alternative terms include ‘bed sore’ and ‘decubitus ulcer.’ The record is kept for occurrences of new pressure areas regardless of their staging or severity.
**Unintentional weight loss**	Weight loss is captured for unintentional weight loss of over 2 kg in any given month. A baseline weight measurement on a specified day within the month needs to be taken before commencing data collection, and then the person is reweighed every month from that date to assess unintentional weight loss. Where a client is on a weight loss diet, due to health reasons, they are not included in this data capture, as we are interested in only unplanned/unintentional weight loss.
**Hospital admissions**	The number of unplanned client transfers (not the number of clients) to hospital where the client has been admitted to hospital. This refers to an unexpected admission for an unexpected event. For example, fracture of neck of femur, post fall, chest infection. This excludes admission to hospital for management of a chronic disease or condition or elective surgery.

NB: The rates are calculated as the total number of new events over six months divided by the mean clients over six months per site.

Economic data (information on the resources used) for implementing the CLiAC program were supplied by the collaborating organisation as aggregate data for all intervention sites using a standardised template. Key items included the program facilitator’s time, teaching materials, and travel costs. Other costs associated with managers participating in the CLiAC program (*e.g*., manager’s time away from their usual work unit and travel) will not be included in the main economic analysis, as they have already been absorbed in the organisation’s usual costs for education and training.

